# Effects of magnesium citrate, magnesium oxide and magnesium sulfate supplementation on arterial stiffness in healthy overweight individuals: a study protocol for a randomized controlled trial

**DOI:** 10.1186/s13063-019-3414-4

**Published:** 2019-05-28

**Keywords:** Magnesium supplements, Arterial stiffness, Blood pressure, Gut microbiota, Randomized controlled trial

## Abstract

**Background:**

Arterial stiffness is closely related to the process of atherosclerosis, an independent cardiovascular risk factor, and predictive of future cardiovascular events and mortality. Recently, we showed that magnesium citrate supplementation results in a clinically relevant improvement of arterial stiffness. It remained unclear whether the observed effect was due to magnesium or citrate, and whether other magnesium compounds may have similar effects. Therefore, we aim to study the long-term effects of magnesium citrate, magnesium oxide and magnesium sulfate on arterial stiffness. In addition, we aim to investigate possible underlying mechanisms, including changes in blood pressure and changes in gut microbiota diversity.

**Methods:**

In this randomized, double-blind, placebo-controlled trial, a total of 162 healthy overweight and slightly obese men and women will be recruited. During a 24-week intervention, individuals will be randomized to receive: magnesium citrate; magnesium oxide; magnesium sulfate (total daily dose of magnesium for each active treatment 450 mg); or placebo. The primary outcome of the study is arterial stiffness measured by the carotid–femoral pulse wave velocity (PWV_c–f_), which is the gold standard for quantifying arterial stiffness. Secondary outcomes are office blood pressure, measured by a continuous blood pressure monitoring device, and gut microbiota, measured in fecal samples. Measurements will be performed at baseline and at weeks 2, 12 and 24.

**Discussion:**

The present study is expected to provide evidence for the effects of different available magnesium formulations (organic and inorganic) on well-established cardiovascular risk markers, including arterial stiffness and blood pressure, as well as on the human gut microbiota. As such, the study may contribute to the primary prevention of cardiovascular disease in slightly obese, but otherwise healthy, individuals.

**Trial registration:**

ClinicalTrials.gov, NCT03632590. Retrospectively registered on 15 August 2018.

**Electronic supplementary material:**

The online version of this article (10.1186/s13063-019-3414-4) contains supplementary material, which is available to authorized users.

## Background

Magnesium is an essential mineral that acts as a cofactor in hundreds of enzymatic reactions in the human body. It is, therefore, not surprising that insufficient magnesium intake has been associated with a wide variety of metabolic disorders, such as insulin resistance, and common diseases that may result from metabolic deregulations, such as hypertension and ischemic heart disease [1–5]. Foods with relatively high magnesium contents include whole grains, leafy green vegetables, legumes and nuts.

Arterial stiffness is closely related to the extent of atherosclerosis [6], an independent cardiovascular risk factor [7], and predictive of future cardiovascular events and mortality [8]. The gold standard for quantifying arterial stiffness is the carotid–femoral pulse wave velocity (PWV_c–f_), a noninvasive method that measures the propagation of the forward pressure wave traveling along the aorta [8]. Recently, we observed a significant reduction of arterial stiffness, measured by the PWV_c–f_, after 24 weeks of oral magnesium citrate supplementation (total daily dose of 350 mg) in the magnesium citrate group compared with the placebo group (8.3 m/s vs 9.1 m/s, respectively) [9]. Although blood pressure is a major determinant of arterial stiffness [10], we did not observe any change in blood pressure. This lack of effect on blood pressure could be due to the total daily dose, which may have been too low to detect changes in blood pressure. A meta-analysis by Kass *et al.* [11] indeed showed that supplementation of > 370 mg/day resulted in a more pronounced blood pressure-lowering effect. In addition, we could not differentiate whether the beneficial effect on arterial stiffness was due to the supplementation of magnesium or due to citrate. The mechanism by which magnesium decreases arterial stiffness is not entirely known, but an effect on gut microbiota has been observed [12–14]. Previous studies have shown that magnesium deficient diets resulted in an altered microbiome and, more specifically, decreased microbial diversity in mice [13, 15, 16]. Gut microbiome diversity has recently been shown to be inversely associated with arterial stiffness, independent of obesity-related traits, such as insulin and visceral fat [17].

The primary aim of the current study is to replicate the effect of magnesium citrate on arterial stiffness that we found in our previous study. Secondly, we aim to test whether magnesium oxide and magnesium sulfate are noninferior to the effect of magnesium citrate on arterial stiffness and to unravel possible underlying mechanisms, including changes in blood pressure and gut microbiota diversity and metabolites.

## Methods/design

### Trial design

In this randomized, double-blind, placebo-controlled trial, healthy overweight and slightly obese volunteers will be allocated to one of the three magnesium groups or the placebo control group. This study will be conducted at the University Medical Center Groningen (UMCG). The current protocol was written in accordance with the Standard Protocol Items: Recommendations for Interventional Trials (SPIRIT) guideline (Fig. 1 and Additional file 1) [18]. Ethics committee approval was obtained from the UMCG, the Netherlands.

**Fig. 1 Fig1:**
[figure not shown]
Schedule of enrolment, interventions and assessment. PWV_c–f_ carotid-to-femoral pulse wave velocity, PHQ-15 Patient Health Questionnaire

### Characteristics of participants

For the present study, only subjects who provide written informed consent are eligible. Furthermore, participants should be between 45 and 75 years and should be overweight or slightly obese (body mass index between 25 and 35 kg/m^2^), because these subjects are expected to have increased arterial stiffness and blood pressure at baseline, allowing for improvement by the intervention [19]. To avoid any possible variations in the study outcomes due to hormonal effects, only postmenopausal women (≥ 2 years after last menstruation) will be included. Participants who meet any of the following criteria are not eligible for this study:high magnesium intake (defined as urinary magnesium excretion of ≥ 7.0 or ≥ 5.9 mmol/24 h for men and women, respectively);plasma glucose ≥ 7.0 mmol/l;serum total cholesterol ≥ 8.0 mmol/l;serum triglycerides ≥ 2.2 mmol/l;current smoker or smoking cessation < 12 months;presence of diabetes mellitus;familial hypercholesterolemia;abuse of drugs;more than 21 alcoholic consumptions per week;unstable body weight (weight gain or loss > 3 kg in the past 3 months);use of proton pump inhibitors;use of lipid-lowering drugs and/or antihypertensive therapy that started in the past 6 months;use of magnesium supplements or an investigational product within another biomedical within the previous 1 month;severe medical conditions that might interfere with the study, such as epilepsy, asthma, kidney failure or renal insufficiency, chronic obstructive pulmonary disease, inflammatory bowel diseases, autoinflammatory diseases and rheumatoid arthritis;active cardiovascular disease; ornot willing to give up being a blood donor (or having donated blood) from 8 weeks before the start of the study and during the study.

### Interventions

The overweight and slightly obese participants will be randomly assigned to receive: magnesium citrate; magnesium oxide; magnesium sulfate; or placebo. A flow chart of the study interventions is presented in Fig. 2. Study participants will be requested to take 2 capsules thrice daily for 24 weeks. On the test days, the first 2 capsules will be taken after all measurements are completed. Each magnesium supplement provides 75 mg magnesium (Magnesium Citrate Complex (Mg 15.5%) Magnesium Sulphate Complex (17.4%) and Magnesium Oxide Complex (60.3%); AMT Laboratories Inc.). Thus, daily magnesium intake provided by the 6 capsules will be 450 mg. The placebo capsules will contain starch (Amylum solani). The total treatment duration of 24 weeks is based on our previous study that showed a significant effect of magnesium supplementation on arterial stiffness after 24 weeks [9]. At baseline and weeks 2, 12 and 24, participants will undergo PWV_c–f_, office blood pressure and body composition measurements. Prior to each test day, participants will collect 24-h urine and fecal samples. In addition, participants will be requested to complete the Patient Health Questionnaire (PHQ-15) before each test day. The PHQ-15 is a somatic symptom subscale derived from the full PHQ. This questionnaire includes about 15 somatic symptoms or symptom clusters that account for more than 90% of the physical complaints reporting in the outpatient setting [20]. Finally, subjects will record any signs of illness in diaries, as well as medication used, and any deviations from the protocol during the study. Subjects are requested not to change their physical activity level, their food intake pattern or use of alcohol during the entire study.

**Fig. 2 Fig2:**
[figure not shown]
Flow chart of the study design

### Blinding and randomization

To ensure the double-blind design, optically similar capsules will be packed and coded by laboratory Medisan (Heerenveen, the Netherlands), who will provide the study medication (magnesium supplements and placebo). In addition, this laboratory will conduct the randomization procedure. For this, they will create a categorical list in logical order. This list will include one intervention for each subject. Based on a computer-generated list of random number, subjects will be randomized into one of the groups. This results in a randomized list of treatment allocation.

### Sample size calculation

The current study is powered on arterial stiffness, the primary endpoint. The required sample size for noninferiority testing is calculated based on a margin of 0.5 m/s, a probability of 0.05 and a power of 0.80. Therefore, 41 subjects per magnesium group are needed. To compare magnesium citrate with placebo, we assume that the number of subjects per group calculated for a two-arm trial (*n* = 24) is sufficient. Because a 10% dropout rate is expected, 162 will be recruited to start the study. By taking into account that only 50% of the subjects included in the screening will meet all inclusion criteria and are willing to participate, 324 subjects are expected to participate in the screening visits.

This sample size calculation is based on an intra-subject variability of 0.9 m/s and a 1.0 m/s change in the PWV_c–f_ after 24 weeks of magnesium supplementation found in our previous study [9]. The equivalence margin of 0.5 m/s is based on the observed effect [9], which is 50% of the magnesium citrate supplementation effect compared to placebo. For the calculation of the sample size, the formula of Julious [21] was used.

### Compliance to the intervention

Compliance will be assessed based on the number of returned capsules after 12 and 24 weeks. Subjects will be considered compliant when they take at least 80% of the capsules. In addition, we will assess compliance by urinary magnesium concentrations at the end of the study.

### Main outcome

The PWV_c–f_ will be recorded in duplicate using the SphygmoCor v9 (AtCor Medical, West Ryde, Australia). First, the distance from the suprasternal notch to the femoral recording site (via umbilicus) will be measured [22]. Subsequently, the distance from the suprasternal notch to the carotid recording site (right) will be subtracted. In addition, the direct distance between the carotid recording site and the femoral recording site (right) will be measured. Second, ECG electrodes will be applied in order to identify the R-wave in the ECG complex. Then, using the tonometer, the arrival of the pulse wave and the delay to the R-wave of the ECG will be measured at the carotid and femoral arteries. If all correct measures are entered and recorded, the program of the manufacturer will calculate the PWV_c–f_ automatically. Using the same tonometer applied to the radial artery near the wrist of the right arm, pulse wave analysis (PWA) will be determined. Measurements are synchronized beat to beat and will be recorded in duplicate. From these recordings, the program of the manufacturer will determine the central augmentation index adjusted for heart rate (CAIxHR75) automatically.

### Secondary outcomes

#### Blood pressure

Office blood pressure (systolic and diastolic) and heart rate will be monitored using a continuous blood pressure monitoring device (Criticare 506 N3; Criticare Systems Inc., Waukesha, WI, USA). The investigator will measure the blood pressure before the PWV_c–f_ measurements. After an acclimatization period of at least 15 min in the supine position, office blood pressure will be measured. The first measurement will be discarded, and the mean of the last three measurements will be reported [23].

#### Gut microbiota

Subjects will be asked to collect a fecal sample 1 or 2 days prior to the test day and store the sample in the fridge at home. They will be asked to bring the sample to the UMCG on ice (cooling elements or in a bag with ice cubes). On the test day, the samples will be immediately stored at − 80 °C. We will investigate the microbiome diversity, specific operational taxonomy as well as specific circulating metabolites, including phenylacetylglutamine, trimethylamine oxide (TMAO) and indoleproprionate (IPA), which have been previously linked to cardiovascular events and metabolic syndrome, respectively [24, 25]. The composition of the gut microbiota in fecal samples will be analyzed with PCR amplification of the 16S rRNA V4–V5 variable region and deep sequencing using the Illumina® MiSeq platform.

#### Anthropometric measurements

On each test day, anthropometric measurements (body weight without shoes and heavy clothing and body composition) will be performed to characterize participants. Body composition (e.g. fat mass, lean body mass, extracellular water and intracellular water) will be measured by Bio-Electrical Impedance Analysis (Bodystat Quadscan 4000®; Quadscan, Douglas, Isle of Man, UK). The measurements will be carried out with the patient in the supine position for 5 min, with their arms parallel to and separated from the trunk and their legs apart. The electrode sites will be cleaned with an alcohol wipe. Two electrodes will be placed on the right hand and wrist, and another two on the right foot and ankle.

#### Patient Health Questionnaire

Participants will be requested to complete the Patient Health Questionnaire (PHQ-15) before each test day. The PHQ-15 is a somatic symptom subscale derived from the full PHQ. This questionnaire includes about 15 somatic symptoms or symptom clusters that account for more than 90% of the physical complaints reporting in the outpatient setting [20].

#### Clinical chemistry

Blood samples will be analyzed at the Department of Laboratory Medicine of the UMCG, according to routine procedures: plasma levels of magnesium, sodium, potassium, chloride, calcium, phosphate, urea, total protein, albumin, creatinine and hemoglobin, hematocrit, leukocytes, thrombocytes and metabolic risk markers (triglycerides, total cholesterol, LDL-cholesterol and HDL-cholesterol, fasting plasma glucose and HbA1C) will be measured. In addition, urinary calcium, sodium, potassium, chloride and creatinine will be determined. To determine the magnesium status, plasma magnesium levels and intra-erythrocyte magnesium will be measured according to routine procedures.

#### Dietary intake

To ensure that participants have maintained their food pattern during the study, subjects are asked to report their diet for 3 consecutive days at the start and at the end of the study in dietary diaries using standard supply units [26]. These diaries will be checked for completeness by the investigator.

### Statistical analysis

For normally distributed parameters, data will be presented as the mean value and standard deviation. Nonnormally distributed parameters will be presented as the median (range). For statistical analyses, responses will be calculated defined as the difference between follow-up and baseline values. For the primary analyses, in which the effect of magnesium citrate on arterial stiffness will be evaluated, differences in responses between magnesium citrate and placebo will be tested (one-factor ANCOVA) with use of the baseline measurements of the outcome variables as covariates. In order to test as secondary analyses whether the effect of magnesium oxide and magnesium sulfate on arterial stiffness are noninferior to the effect of magnesium citrate on arterial stiffness, a noninferiority margin (Δ) of 0.5 m/s is chosen based on the effect size of magnesium citrate on arterial stiffness found in previous research [9]. A one-factor ANCOVA, with use of the baseline measurements of the outcome variables as covariates, will be conducted to evaluate differences in responses between magnesium and placebo treatments. To prove noninferiority, the lower limit of the confidence interval of the difference between magnesium sulfate and magnesium citrate and the difference between magnesium oxide and magnesium citrate must not exceed the limit of Δ to be 95% sure that magnesium oxide and magnesium sulfate are not worse than magnesium citrate supplements by more than Δ. Treatment effects will be calculated at each time point (after 2, 12 and 24 weeks) with one-factor ANCOVA. Differences are considered statistically significant at *P* < 0.01 for the primary analyses (confirmatory) and *P* < 0.05 for the secondary analyses (exploratory). Statistical analyses will be performed using SPSS 23.0 software for Windows (SPSS Incorporated, Chicago, IL, USA). Normality of the residuals will be examined using the Shapiro–Wilk normality test. If a residual is not normally distributed, parameters will be log-transformed. If after log-transformation the residuals are still not normally distributed, nonparametric tests will be used. Missing data will not be replaced by estimates. Because of randomization, it is expected that confounders will be divided equally. Therefore, no adjustment for confounding will take place. The intention-to-treat principle will be applied in primary analyses. Secondly, we will conduct per-protocol analyses (exclude noncompliance subjects from the statistical analysis). To prove noninferiority, the confidence interval of the difference must exclude the margin in both the intention-to-treat and the per-protocol analyses. Finally, we will conduct subgroup analyses in which we will compare the effects of magnesium on arterial stiffness in subjects on antihypertensive therapy and subjects not on antihypertensive therapy. Because over time arterial stiffness may increase more rapidly in subjects treated for hypertension, our hypothesis is that magnesium may have a more pronounced effect on arterial stiffness in subjects on antihypertensive therapy.

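### If the normality rule fires for PWV, the analysis leaves the m/s scale, and the 0.5 m/s noninferiority margin has no stated counterpart on the log or rank scale

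*Protocol article*

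**What the plan says.** All of the rules stand in the Statistical analysis section of the protocol article.

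- **Analysed variable:** "responses will be calculated defined as the difference between follow-up and baseline values". A fall in PWV is therefore a negative number.
- **Model:** "A one-factor ANCOVA, with use of the baseline measurements of the outcome variables as covariates".
- **Trigger:** "Normality of the residuals will be examined using the Shapiro–Wilk normality test".
- **First fallback:** "If a residual is not normally distributed, parameters will be log-transformed".
- **Second fallback:** "If after log-transformation the residuals are still not normally distributed, nonparametric tests will be used".
- **Margin:** "a noninferiority margin (Δ) of 0.5 m/s is chosen based on the effect size of magnesium citrate on arterial stiffness".
- **Noninferiority decision:** "the confidence interval of the difference must exclude the margin in both the intention-to-treat and the per-protocol analyses".

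The fallback is not limited to particular outcomes, so it covers PWV. The Sample size calculation section sizes the magnesium groups on the same untransformed scale: "a margin of 0.5 m/s, a probability of 0.05 and a power of 0.80", with a variability of 0.9 m/s and an expected change of 1.0 m/s, giving 41 per magnesium group. The article gives no ratio margin for log PWV, no back-transformation and no rank-based confidence interval.

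**The concern.** The noninferiority rule needs a confidence limit for a difference in m/s. Each fallback step replaces the analysis that supplies one with an analysis that, as written, does not. Whether the comparison with the margin can be made at all then depends on a preliminary test of the residuals.

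Three things are at stake:

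- Oxide and sulfate would be compared with citrate on a scale for which no margin was set, or a margin would have to be invented after the data were seen.
- The intention-to-treat and per-protocol sets have different residuals, so one could pass Shapiro–Wilk and the other fail. They would then be on different scales although both must exclude the same margin.
- For the confirmatory citrate–placebo comparison, the scale and the effect measure would be picked by the data.

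**Working it through.** **1. Reproduce the plan's figure on the m/s scale.** Inputs from Sample size calculation: margin 0.5, SD 0.9, power 0.80; a true difference of 0 is assumed. The sidedness of the 0.05 is not stated.

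n = 2 × [0.9 × (1.645 + 0.842) / 0.5]² = 40.06, rounded up to 41.

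One-sided 0.025 would give 51, so 41 corresponds to one-sided 0.05. Power at 41 per group by the noncentral t is 80.2%. The design is coherent as long as the analysis stays in m/s.

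**2. First fallback applied to the responses.** Assume normal changes with mean −1.0 m/s in a magnesium arm. The share at or below zero, which has no logarithm, is Φ(1.0 / SD of change):

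- 0.9 read as the SD of change: Φ(1.111) = 0.867.
- 0.9 read as a per-visit SD: SD of change = 0.9 × √2 = 1.27, and Φ(0.786) = 0.784.

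In a noninferiority pair of 82 subjects, that is 82 × 0.784 ≈ 64 to 82 × 0.867 ≈ 71 responses lost, and they are the subjects who did not worsen. In placebo the share is 50% if the mean change is 0 (assumption).

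**3. First fallback applied to raw PWV.** The log exists, but the contrast is a ratio. The Background section gives 8.3 and 9.1 m/s as PWV levels in the previous study.

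- At 8.3 m/s: 8.8 / 8.3 = 1.060.
- At 9.1 m/s: 9.6 / 9.1 = 1.055.
- At assumed levels of 7 and 11 m/s: 7.5 / 7 = 1.071 and 11.5 / 11 = 1.045.

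Conversely, a fixed ratio of 1.060 amounts to 0.42 m/s at 7 m/s and 0.66 m/s at 11 m/s. No single ratio equals 0.5 m/s across the range.

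**4. Second fallback.** An ordinary rank test of no difference does not answer a noninferiority question. A rank method could do so if it were specified. A margin-shifted Mann–Whitney test, simulated at 41 per group with normal data and SD 0.9 (4,000 runs), had about 78% power against 80% for the t-test, and type I error of about 5% for both. The article names no such method.

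**5. How often the rule would fire.** No document gives the skewness of the residuals, and the article sets no level for Shapiro–Wilk. Simulated rejection rates, assuming a 5% level, for n = 65 (41 + 24) and n = 147 (3 × 41 + 24):

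| Assumed skewness | n = 65 | n = 147 |
|---|---|---|
| 0 | about 5% | about 5% |
| 0.2 | 10% | 13% |
| 0.3 | 13% | 23% |
| 0.5 | 28% | 58% |
| 0.7 | about 50% | about 89% |

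The rates at 0.5 and 0.7 use gamma-distributed residuals. They are for the first trigger only; no rate was computed for a second failure after logging.

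**6. Whether the switch is needed.** With gamma data at skewness 0.7–1.0, the ordinary t comparison kept its error rate: 0.93–1.0% at a nominal two-sided 1% (41 against 24) and 4.9–5.1% at a nominal 5% for noninferiority (41 against 41). Under skewness of this order the switch gives up an analysis that was still sound.

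**The case against.** A reader might infer that the plan logs change scores, that most of the data would be lost, and that the primary result could then not be computed. The document does not support this.

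- The article says that *parameters* are logged. It calls the changes *responses* and elsewhere uses *parameters* for the data to be presented. Logging raw PWV, which is always positive, is at least as plausible. The 78–87% applies to one of two readings.
- The primary citrate–placebo comparison is a superiority test and uses no margin. ANCOVA on log PWV, or a rank test, would still decide it. What changes is the effect measure.
- The nonparametric test is unnamed, so it cannot be said that it must drop the baseline covariate. Rank ANCOVA keeps it, and a Hodges–Lehmann interval on the responses is in m/s.
- High trigger rates rest on assumed skewness. With near-normal residuals the rule seldom fires, and when it does not, the stated ANCOVA uses the margin coherently.
- Noninferiority is classed as secondary and exploratory, a check-then-transform rule is conventional, and the choice of rank method can be left to a fuller plan.

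All of this narrows the point. What remains is that the raw-PWV reading also removes the m/s margin, and that the article states a rule which, when followed, takes the analysis off the scale its own decision rule requires. That goes beyond an omitted detail. Noninferiority, although secondary, also sets the size of the three magnesium groups: 3 × 41 = 123 of the 147 planned completers.

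**Conclusion.** The point holds, conditional on the rule being triggered, and mainly for noninferiority. After either fallback step the 0.5 m/s margin has no stated counterpart: logs of non-positive changes do not exist, logs of PWV give a ratio, and no rank-based interval in m/s is named. The citrate–placebo test remains computable on logged levels or ranks, but its scale would depend on the data.

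The share of responses without a logarithm rests on normal changes with the planned mean of −1.0 m/s and on which SD the 0.9 denotes. The chance of triggering runs from about 5% (normal residuals) to as much as 89% (skewness 0.7, n = 147), and the document does not allow it to be narrowed. Calling the margin unusable would go too far, because a specified rank-based shift interval could retain it. Severity: should-fix.

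**What to change.** For PWV, remove the switch. State that baseline-adjusted ANCOVA on the m/s scale is used for the primary and the noninferiority analyses, in both the intention-to-treat and the per-protocol sets, whatever Shapiro–Wilk shows. Add one sensitivity analysis that yields an interval in m/s: bootstrap, heteroscedasticity-robust or Hodges–Lehmann. Limit log-transformation to skewed, positive secondary variables, modelling log follow-up on log baseline and never logging a change. If a log analysis of PWV is wanted all the same, its ratio margin must be set and justified in advance.

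The cost is a few sentences and one extra analysis run. The 41 per magnesium group is unchanged. The text should be settled before unblinding, since a later choice of scale would itself be driven by the data.

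### Beyond baseline PWV, the plan bars covariate adjustment for a reason that ignores precision and does not cover the per-protocol noninferiority analysis

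*Protocol article*

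**What the plan says.** The Statistical analysis section of the protocol article plans one-factor ANCOVAs on change from baseline, "with use of the baseline measurements of the outcome variables as covariates". It says this for citrate versus placebo and again for the comparisons behind the noninferiority test. Later in the same section it excludes other covariates: "Because of randomization, it is expected that confounders will be divided equally. Therefore, no adjustment for confounding will take place".

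Noninferiority must be shown in both the intention-to-treat and the per-protocol analysis, and the latter leaves out noncompliant subjects.

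Two statements name factors that may matter for the outcome. The Background says that "blood pressure is a major determinant of arterial stiffness". The rationale for the subgroup analysis by antihypertensive therapy says that "over time arterial stiffness may increase more rapidly in subjects treated for hypertension".

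**The concern.** The exclusion is a stated decision, so a later analysis plan could not add covariates without contradicting it. The reason given has two gaps.

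- **Precision.** Expected balance bears on bias. The usual reason to adjust in a randomized trial is to remove outcome variance that baseline factors explain, and the sentence does not address this. The noninferiority comparisons are planned at 80% power, so they have the least slack.
- **The per-protocol set.** Randomization supports expected balance among everyone randomized. It gives no such assurance once subjects are removed for what they did afterwards. Noninferiority depends on this set too, and the same sentence bars adjustment there.

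At stake are intervals wider than they may need to be, and a per-protocol result with no prespecified adjustment beyond baseline PWV.

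**Working it through.** **Inputs from the Sample size calculation section.** Noninferiority uses "a margin of 0.5 m/s, a probability of 0.05 and a power of 0.80", and "41 subjects per magnesium group are needed". For citrate versus placebo, the number "calculated for a two-arm trial (*n* = 24) is sufficient". Both are "based on an intra-subject variability of 0.9 m/s and a 1.0 m/s change". The primary test uses P < 0.01 (Statistical analysis), taken here as two-sided. The 0.9 m/s is taken as the residual SD once baseline PWV is in the model.

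**Assumed.** The share R² of that residual variance explained by four further covariates is not given. The range used is 0.05 to 0.20, with 0 as the worst case.

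**Reproducing the plan.**
- Noninferiority: 2 × (0.9/0.5)² × (1.645 + 0.842)² = 40.1, so 41 per arm. This matches if the 0.05 is one-sided; one-sided 0.025 would need 51.
- Citrate versus placebo: 1.0 m/s, SD 0.9, two-sided 0.01 and 90% power give 25, close to 24. The article does not state the error rate and power behind 24, so this match is only indicative.
- Total: 3 × 41 + 24 = 147, and 147 × 1.1 = 161.7, so 162.

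**Effect of further covariates.** The residual SD becomes 0.9 × √(1 − R²), and SE = SD × √(1/n₁ + 1/n₂). Power is from the noncentral t distribution. Degrees of freedom are n₁ + n₂ − 3 as planned (79 for 41 vs 41, 62 for 41 vs 24) and four fewer with the added covariates.

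| Model | SE, 41 vs 41 | Noninferiority power | SE, 41 vs 24 | Power at 1.0 m/s | Power at 0.8 m/s |
|---|---|---|---|---|---|
| As planned | 0.199 | 80.2% | 0.231 | 94.8% | 78.5% |
| R² = 0 | 0.199 | 80.2% | 0.231 | 94.8% | 78.3% |
| R² = 0.05 | 0.194 | 81.9% | 0.225 | 95.8% | 80.8% |
| R² = 0.10 | 0.189 | 83.7% | 0.219 | 96.8% | 83.3% |
| R² = 0.20 | 0.178 | 87.3% | 0.207 | 98.3% | 88.1% |

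The 0.8 m/s is the difference between the previous trial's group values in the Background (9.1 − 8.3). In sample-size terms the gain is 41/0.95 − 41 = 2.2 to 41/0.80 − 41 = 10.3 subjects per magnesium arm.

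**Cost.** Counting degrees of freedom alone, four useless covariates cost under 0.2 points of power (the R² = 0 row). The table leaves out a second cost: covariates that differ between arms by chance inflate the variance of the contrast. For normal covariates the average factor is (f − 1)/(f − 1 − q), where f is the error degrees of freedom before covariates and q the number of covariates. Going from q = 1 to q = 5:
- 41 vs 41 fitted alone (f = 80): 78/74 = 1.054. The variance ratio is 0.95 × 1.054 = 1.00 at R² = 0.05 and 0.80 × 1.054 = 0.84 at R² = 0.20.
- 41 vs 24 fitted alone (f = 63): 61/57 = 1.070, giving 1.02 and 0.86.
- One model on all four arms (f = 143): 141/137 = 1.029, giving 0.98 and 0.82.

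So R² = 0.05 is about break-even in a two-arm fit and a small gain in a four-arm fit. R² = 0.10 or more is a gain in every case.

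**The case against.** The strongest reply is that nothing is broken. The analysis already adjusts for baseline PWV, normally the most prognostic covariate for change in PWV. Prespecifying no other covariate is legitimate: under intention to treat the estimate is unbiased and the type I error is kept. All of that stands.

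A reader might infer that the plan rules out covariate adjustment altogether. It does not; the excluding sentence sits beside an ANCOVA on baseline PWV.

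A reader might also infer that chance imbalance in a placebo arm of about 24 would bias the primary contrast. The spread of a standardized baseline difference is √(1/41 + 1/24) = 0.26 SD, a 95% range of about ±0.50 SD. That is random error which the standard error already carries. For therapy status at an assumed 30% prevalence the range is about ±23 percentage points. If treated and untreated subjects differed in 24-week change by an assumed 0.2 m/s, an imbalance that large would move the contrast by 0.23 × 0.2 = 0.05 m/s; at an assumed 0.5 m/s it would be 0.12. The standard error is 0.23.

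Nor does the article show that blood pressure or therapy strongly predicts 24-week change once baseline PWV is in the model. The Background speaks of the level of stiffness, which baseline PWV partly carries. The remark on treated subjects is a hedged reason for a subgroup hypothesis, with no size given. The choice of covariates is therefore a reasonable one that the documents do not compel.

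Finally, the primary comparison has little to gain at the planned 1.0 m/s, where power is already about 95%. That is correct, and it places the benefit mainly in the noninferiority comparisons.

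The reply leaves two things unanswered: the stated reason says nothing on precision, and it does not extend to the per-protocol analysis.

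**Conclusion.** The point holds as one of efficiency and robustness. The planned intention-to-treat analysis is valid and no bias is being corrected there. The exclusion of further covariates rests on a reason that misses precision and does not reach the per-protocol set, where adjustment can lessen imbalance in measured factors but cannot undo selection on unmeasured ones.

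The benefit lies mainly in the two noninferiority comparisons: about 2 to 7 points of power over the assumed R² range, before the average cost of covariate imbalance. For the primary comparison it is about 1 to 3.5 points at 1.0 m/s and 2 to 10 at 0.8 m/s. These sizes depend on an R² that the article does not give. At the low end the net gain may be nil if only two arms are fitted.

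**What to change.** Replace the sentence that excludes adjustment. State, before unblinding, that the PWV ANCOVAs (primary and noninferiority, intention-to-treat and per-protocol) include baseline PWV plus a short fixed set of baseline covariates: age, sex, baseline blood pressure and antihypertensive therapy (yes/no). Keep the model with baseline PWV alone as a sensitivity analysis. Estimating the covariate slopes from all four arms in one model keeps the imbalance cost low.

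No new data are needed. Blood pressure is measured at baseline, age and sex enter the eligibility criteria, and therapy status is required for the planned subgroup analysis. The cost is a change of wording, about four degrees of freedom (under 0.2 points of power if the covariates explain nothing), and the average variance inflation shown in the working, about 3% in a four-arm fit and 5 to 7% in a two-arm fit.
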